### Who will take informed consent?

During the preoperative visit, on arrival at the hospital department the day before surgery, one of the trial members who has a medical doctor’s license will explain the study protocol and obtain written informed consent from the patients or their guardians. On the day of surgery, the investigating physician will collect the signed consent form after ensuring that the patient has understood the information leaflet and recheck the inclusion and exclusion criteria.

### Additional consent provisions for collection and use of participant data and biological specimens

There are no plans for the use of participants’ data and biological specimens in ancillary studies.

## Interventions

### Explanation for choice of comparators

Patients will be randomly assigned to one of four groups: pregabalin 25 mg, 50 mg, 75 mg, or placebo. Placebo was chosen as an appropriate comparator because the intervention is proposed as an adjunct to routine postoperative pain control. Currently, there are no recommendations for routine perioperative analgesia.

### Intervention description

Patients will be allocated into one of four groups: placebo group (P0), pregabalin (Kabalin; HK inno.N Corp., Seoul, South Korea) 25 mg group (P25), pregabalin 50 mg group (P50), and pregabalin 75 mg group (P75) [18]. The P0 group will take three placebo capsules once prior to surgery and every 12 h after surgery for 72 h. The P25 group will take one 25 mg pregabalin capsule and two placebo capsules, the P50 group will take two 25 mg pregabalin capsules and one placebo capsule, and the P75 group will take three 25 mg pregabalin capsules, all according to the same schedule. The 25 mg pregabalin capsule and placebo capsule will have the same appearance for blinding.

### Criteria for discontinuing or modifying allocated interventions

Participants who present with severe drowsiness, dizziness, visual disturbance, or swelling that precludes the use of pregabalin will discontinue the trial and stop taking their allocated treatment. Participants who develop infection, nerve injury, hematoma, or metal-related complications following surgery or those who request discontinuation will also be excluded from the trial.

### Strategies to improve adherence to interventions

Participants will be directly observed taking their medications by clinical nurses and clinical research associates (CRAs) at the study sites to encourage and monitor adherence.

### Relevant concomitant care permitted or prohibited during the trial

After the surgical procedure, IV PCA (PS-1000; Unimedics, Seoul, Korea) will be administered and continued for 72 h. The PCA regimen will consist of fentanyl 1500 μg (total volume including saline: 150 mL) and will be administered at 2 mL/h as background infusion and 2 mL on demand with a 30-min lockout.

Concomitant therapy for comorbidities, such as hypertension, diabetes, rheumatoid arthritis, etc., will be permitted and documented. Any analgesic use is prohibited from 48 h before surgery until 72 h after surgery. If the participant asks for additional pain control, rescue analgesics, including oxycodone (IRcodon tab 5 mg; Unimed, Seoul, Korea), fentanyl patch (Durogesic patch 12 μg/h; Janssen Korea, Seoul, Korea), or pethidine (Pethidine 25 mg injection; Hana Pharm Co., Seoul, Korea), will be administered.

If participants present with nausea or vomiting, ramosetron (Nasea Injection 0.3 mg/2 ml; Daiichi Sankyo, Seoul, Korea) will be administered intravenously. If symptoms continue after ramosetron administration, metoclopramide (Macperan Injection 10 mg/2 ml; Dong Wha Pharm Co., Seoul, Korea) will be administered intravenously.

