### Outcomes

We will examine the efficacy of pregabalin on postoperative pain using the variables described in the literature [12]. The primary outcomes are pain intensity measured on a visual analogue scale (VAS) (length, mm), total administered amount of IV PCA measured (volume, mL), and frequency of rescue analgesics administered (the number of administrations, according to the type of rescue analgesic, and the total amount of morphine equivalent dose). The VAS score is evaluated using a pain ruler marked from 0 (no pain) to 100 (maximal pain) mm, with patients directly indicating their pain level. The secondary variables are the incidence and frequency of nausea and vomiting caused by IV PCA. Assessments of all variables will be performed during the first 72 h following the arrival of the participant at the general ward, subdivided into four periods: 1–6 h, 6–24 h, 24–48 h, and 48–72 h. We will evaluate pain between the midpoint and the end of each of the four time zones, aiming to measure as close to the end time as possible and use the pain scores at all four time points as the primary outcome. The pain levels in each time zone will be compared to see if they differ depending on the treatment method. Through this, we will ascertain how the treatment effect changes over time and how these changes differ among different treatment groups. Through these variables, we plan to check the effects of pregabalin on reduction of postoperative pain and IV PCA usage. In addition, we will examine whether reduction of IV PCA usage has a beneficial effect on the patient by reducing the incidences of common side effects, nausea and vomiting.

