### Sample size

The prior calculation of the sample size indicated that at least 28 subjects were required for each group. For calculation, the software G*Power 3.1.9.7 was used with a statistical power of 0.95 at an effect size of 0.448 with an alpha level of 0.0167. The effect size was determined based on a previous study [18]. In this study, three groups—those treated with placebo, pregabalin 75 mg, and pregabalin 150 mg—each comprised 28 participants. The groups were compared based on their PCA usage, with mean values of 95.3, 96.6, and 105.2 respectively, and an approximate standard deviation of 10. For the purposes of this study, which involves four instead of three groups, a fourth hypothetical group was considered with the mean value of 96.6, which is the median value of the three established groups. Based on this data, Cohen’s *f* was calculated, resulting in an effect size of 0.448. To compare the four groups through Bonferroni’s test, the alpha level was set at 0.05 divided by 4, which is 0.0167. When calculated based on these parameters, the total sample size needed is found to be 112, and the number of participants needed per group is 28. Considering a follow-up loss of approximately 15%, 33 participants per group would be required, resulting in a total of 132 participants needed for the study.

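### As printed, one 150 mL PCA fill leaves 6 mL for demand over 72 h; unless reservoirs are replaced, 48–72 h and 72 h total PCA volume cannot be read as opioid need

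*Protocol article*

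**What the plan says.** All the pump settings stand in the section on concomitant care permitted or prohibited. The reservoir holds fentanyl 1500 μg, with "total volume including saline: 150 mL) and will be administered at 2 mL/h as background infusion and 2 mL on demand". The demand setting is "2 mL on demand with a 30-min lockout". IV PCA "will be administered and continued for 72 h". The article does not mention a second reservoir, a refill, or what happens when the pump empties.

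The Outcomes section makes PCA use a primary outcome, as "total administered amount of IV PCA measured (volume, mL", alongside VAS pain and rescue analgesia. It is assessed "during the first 72 h following the arrival of the participant at the general ward". That assessment window is in turn "subdivided into four periods: 1–6 h, 6–24 h, 24–48 h, and 48–72 h". The same section intends to learn whether pregabalin lowers PCA use, and whether lower use reduces nausea and vomiting. PCA use is also the variable behind the Sample size section: "The groups were compared based on their PCA usage".

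**The concern.** A PCA volume measures opioid need only if the pump can deliver what the patient asks for. Here the stated fill is almost the same as 72 h of background infusion, so almost none of it is left for demand. A patient who takes a fourth bolus cannot both stay on that one fill and have PCA for the full 72 h. The printed fill, rate and duration therefore conflict for anyone with more than minimal demand.

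If the fill is not replaced, two of the PCA measures are at stake. The 72 h total becomes nearly constant, so a dose that truly reduces demand could show almost no difference. The 48–72 h volume becomes whatever earlier demand left behind, so the group with less demand can record more PCA. A working dose could then look as if it increased opioid use on the third day.

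**Working it through.** **Inputs**, all from the concomitant-care section: fill 150 mL; background 2 mL/h; bolus 2 mL; lockout 30 min, so at most 2 boluses per hour; duration 72 h. The periods come from Outcomes. The plan gives no expected PCA volume for this regimen, so there is no stated figure to reproduce.

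**Volume balance over 72 h from pump start**
- Background: 2 × 72 = 144 mL.
- Left for demand: 150 − 144 = 6 mL, and 6 / 2 = 3 boluses.
- Allowed by the lockout: 2 × 72 = 144 boluses = 288 mL, so the settings permit up to 144 + 288 = 432 mL against a 150 mL fill.
- With one fill and an unpaused pump, the total lies in 144–150 mL. Two group means cannot differ by more than 6 mL.

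**Which periods are affected (one fill, pump clock)**
- 1–6 h and 6–24 h: maximum delivery is (2 + 4) × 24 = 144 mL by 24 h, below 150. These periods cannot be truncated at any demand.
- 24–48 h: background to 48 h is 96 mL, leaving 54 mL, or 27 boluses. Truncation occurs only above 27 boluses by 48 h.
- 48–72 h: after k boluses by 48 h, 150 − 96 − 2k = 54 − 2k mL remain. A patient with no boluses records 2 × 24 = 48 mL. Since 54 − 2k < 48 when k > 3, anyone with more than three early boluses records less than that patient. Each further early bolus lowers the figure by 2 mL: k = 4 gives 46 mL, k = 12 gives 30 mL.

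**Ward clock.** Outcomes are timed from ward arrival. Suppose the pump starts d hours earlier.
- If PCA runs to ward hour 72, the remainder at ward hour 48 is 54 − 2d − 2k against a background need of 48. The threshold becomes k > 3 − d. At d = 3, background alone uses 2 × 75 = 150 mL.
- If PCA stops at pump hour 72, the need is 48 − 2d and the threshold stays at k > 3.
- For the earlier periods, maximum delivery by ward hour 24 is 6 × (24 + d), which passes 150 mL only if d > 1 and demand is maximal. The 24–48 h threshold becomes 27 − d boluses.

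**Illustration of the reversal.** The document gives no demand rate. Assume constant demand of b boluses per day on placebo, 30% fewer on active drug, and the pump clock. The hourly rate is 2 + 2b/24. Differences are active minus placebo, in mL.

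| Placebo b | 48–72 h, one fill | 48–72 h, replaced |
|---|---|---|
| 1 | 49.4 − 50 = −0.6 | −0.6 |
| 2 | 48.4 − 46 = +2.4 | 50.8 − 52 = −1.2 |
| 4 | 42.8 − 38 = +4.8 | 53.6 − 56 = −2.4 |

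At 2 per day, the 72 h total difference is 150 − 150 = 0 with one fill and 152.4 − 156 = −3.6 with replacement. In the same scenarios the 0–48 h difference keeps its correct sign: 101.6 − 104 = −2.4 at 2 per day and 107.2 − 112 = −4.8 at 4 per day. The sign change follows from the volume balance; the sizes follow from the assumed rates.

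**The case against.** The strongest reply is that the protocol says PCA runs for 72 h. A pump that empties early does not, so replacement is implied. The 150 mL may simply describe how the mixture is made up (1500 / 150 = 10 μg/mL), and reservoir changes are the kind of detail that a journal article leaves to the full protocol. This has force, and replacement does remove the problem entirely. It does not settle the matter, because the stated volume nearly equals 72 h of background. A single fill planned to last three days is at least as natural a reading. The figures in conflict are printed, so this is more than a missing detail.

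The second reply is that much of the evidence survives even with one fill. That is correct. On the pump clock the first two periods are intact and the third is nearly so. VAS and rescue use, both primary, would show part of any unmet need.

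A reader might go further in three ways that the documents do not support:
- That the PCA outcome as a whole is invalid. Only 48–72 h and the 72 h total are at risk, apart from very heavy demand, and only without replacement.
- That the planning values in the Sample size section, "with mean values of 95.3, 96.6, and 105.2 respectively, and an approximate standard deviation of 10", could not arise under this regimen. No unit or time window is given for them. If they were mL over 48 h, one fill would allow 96–150 mL, so no conclusion follows.
- That the reversal has a known size. It rests on assumed demand, and at one bolus per day there is none.

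**Conclusion.** The concern holds conditionally. The printed fill, background rate and duration do not fit a demand-driven primary outcome, and the article does not say how the gap is closed. With a single unreplaced fill and an unpaused pump, total volume from pump start is confined to a 6 mL band, and 48–72 h volume falls as earlier demand rises beyond three boluses. Neither measure can then be read as opioid need, and the 48–72 h comparison can point the wrong way. Those statements need no demand assumption; the sizes in the table are illustrative only. Pausing the pump would lower the 144 mL floor, and a pump started before ward arrival moves the thresholds as shown. Whether reservoirs will be replaced cannot be determined from the article. The point is worth fixing because it touches a primary outcome and costs little to settle.

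**What to change.** In the concomitant-care section, state that an emptied reservoir is replaced with the same mixture so that PCA runs the full 72 h. Record the time of emptying or replacement on the CRF.

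If reservoirs will not be replaced:
- base PCA-volume inference on the periods up to 48 h;
- report total opioid over 0–72 h (PCA fentanyl plus rescue, in morphine equivalents) as the measure of opioid need, in place of 48–72 h and total PCA volume; Outcomes already calls for rescue in morphine equivalents;
- keep patients whose pump emptied in the analysis with their recorded volume. The missing-data section excludes patients with missing data, so coding an empty pump as missing would remove the heaviest users.

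The cost is one sentence, one CRF field and occasional extra fentanyl fills. A fentanyl conversion factor is needed only if reservoirs are not replaced.

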### Provisions for post-trial care

The principal investigator has insurance, in accordance with the legal requirements in South Korea, that provides coverage for any injuries or deaths caused by the study. The insurance covers the injury/death occurring during the study or within 1 year after study completion.

### Outcomes

We will examine the efficacy of pregabalin on postoperative pain using the variables described in the literature [12]. The primary outcomes are pain intensity measured on a visual analogue scale (VAS) (length, mm), total administered amount of IV PCA measured (volume, mL), and frequency of rescue analgesics administered (the number of administrations, according to the type of rescue analgesic, and the total amount of morphine equivalent dose). The VAS score is evaluated using a pain ruler marked from 0 (no pain) to 100 (maximal pain) mm, with patients directly indicating their pain level. The secondary variables are the incidence and frequency of nausea and vomiting caused by IV PCA. Assessments of all variables will be performed during the first 72 h following the arrival of the participant at the general ward, subdivided into four periods: 1–6 h, 6–24 h, 24–48 h, and 48–72 h. We will evaluate pain between the midpoint and the end of each of the four time zones, aiming to measure as close to the end time as possible and use the pain scores at all four time points as the primary outcome. The pain levels in each time zone will be compared to see if they differ depending on the treatment method. Through this, we will ascertain how the treatment effect changes over time and how these changes differ among different treatment groups. Through these variables, we plan to check the effects of pregabalin on reduction of postoperative pain and IV PCA usage. In addition, we will examine whether reduction of IV PCA usage has a beneficial effect on the patient by reducing the incidences of common side effects, nausea and vomiting.

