**Methods:**

This is a prospective, randomized controlled, double-blind study. A total of 132 participants will be randomly assigned to the placebo (*n* = 33) group or to the pregabalin 25 mg (*n* = 33), 50 mg (*n* = 33), or 75 mg (*n* = 33) groups. Each participant will be administered placebo or pregabalin once prior to surgery and every 12 h after surgery for 72 h. The primary outcome will be the visual analogue scale pain score, total dose of administered intravenous patient-controlled analgesia, and frequency of rescue analgesic administered for 72 h from arrival to the general ward after surgery, subdivided into four periods: 1–6 h, 6–24 h, 24–48 h, and 48–72 h. The secondary outcomes will be the incidence and frequency of nausea and vomiting due to intravenous patient-controlled analgesia. Safety will be assessed by monitoring the occurrence of side effects such as sedation, dizziness, headache, visual disturbance, and swelling.

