**Assessments:**								
VAS score				X	X	X	X	X
IV PCA usage				X	X	X	X	X
Frequency of rescue analgesic use				X	X	X	X	X
Frequency of nausea and vomiting				X	X	X	X	X
Sedation				X	X	X	X	X
Dizziness				X	X	X	X	X
Headache				X	X	X	X	X
Visual disturbance				X	X	X	X	X
Swelling				X	X	X	X	X

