## Statistical methods

### Statistical methods for primary and secondary outcomes

The primary objective of this study is to compare the effect of different doses of pregabalin to placebo on pain relief and the need for additional analgesics during the 72-h period following surgery, at various time points. Additionally, the study aims to assess the incidence of adverse events during this period. Primary outcomes include the VAS pain score, total dose of IV PCA administered, and frequency of rescue analgesic administered. We will use the Kolmogorov–Smirnov test (K-S test) to assess the normality of the primary outcome measure. If the normality assumption is met, we will perform an analysis of variance (ANOVA) analysis; otherwise, we will use the Kruskal–Wallis test for comparison. We will use the Bonferroni’s method for conducting subgroup analysis to account for multiple comparisons. Categorical variables, such as the incidence and frequency of nausea and vomiting caused by IV PCA or the incidence of side effects (sedation, dizziness, headache, visual disturbance, and swelling), will be compared between the groups using the chi-squared test. Statistical analyses will be performed using SPSS 20.0 (IBM, Armonk, NY, USA). In all analyses, *P* < 0.05 will be taken to indicate statistical significance.

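### The secondary outcome is limited to nausea and vomiting caused by IV PCA, but Table 2 and the stated aim carry no such limit, and taken literally it needs a subjective attribution made after randomisation

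*Protocol article*

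**What the plan says.** The limit by cause appears in three places in the protocol article.

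- Abstract, Methods: "The secondary outcomes will be the incidence and frequency of nausea and vomiting due to intravenous patient-controlled analgesia".
- Outcomes: "The secondary variables are the incidence and frequency of nausea and vomiting caused by IV PCA".
- Statistical methods for primary and secondary outcomes: the categorical variables compared by chi-squared test include "the incidence and frequency of nausea and vomiting caused by IV PCA or the incidence of side effects".

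Two places carry no such limit. The assessment row in Table 2 reads only "Frequency of nausea and vomiting". The closing sentence of Outcomes gives the aim as learning whether lower PCA use helps patients by making nausea and vomiting less common, with nothing said about cause.

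The side effects named for comparison between groups are "side effects (sedation, dizziness, headache, visual disturbance, and swelling". Nausea and vomiting are not among them. The section on adverse event reporting has every adverse event entered in the case report form.

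**The concern.** A limit by cause is harmless if cause can be determined, or if the words only describe why nausea is expected. The first does not apply here. Every participant has a background fentanyl infusion and takes study capsules every 12 h, and may also receive oxycodone, a fentanyl patch or pethidine. With several possible causes acting at once, assigning an event to PCA is a matter of opinion.

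That opinion would be formed after randomisation, with rescue use in plain view. Rescue use is one of the primary outcomes, so the trial is set up to look for a difference in it between arms. If events are more readily put down to rescue medication where more of it was given, inclusion in the secondary outcome depends on something that treatment may change. The arms would then not be compared on the same basis, even with allocation fully blinded.

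At stake is the interpretation of the only named secondary outcome, and with it the trial's answer on whether sparing PCA spares patients nausea and vomiting.

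**Working it through.** The plan gives no figure for this outcome, so there is none to reproduce. The check has two parts.

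**1. The text side by side**

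| Element | Limited to PCA as cause? |
|---|---|
| Secondary outcome, abstract | Yes |
| Secondary outcome, Outcomes section | Yes |
| Variable analysed, statistical methods | Yes |
| Variable recorded, Table 2 | No |
| Aim, end of Outcomes | No |
| Side effects compared between groups | Nausea and vomiting not listed |

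Taken literally, the variable recorded and the variable analysed differ. Getting from one to the other needs a decision on each event.

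The possible causes overlap in time. Under concomitant care, PCA continues for 72 h after surgery, with a 2 mL/h background infusion plus demand doses. In the same section: "If the participant asks for additional pain control, rescue analgesics, including oxycodone", a fentanyl patch or pethidine are given. The intervention description has study capsules taken before surgery and every 12 h afterwards for 72 h. The patch and the PCA deliver the same drug.

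**2. What attribution does to the comparison**

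Let p0 and p1 be the true all-cause rates on placebo and on a pregabalin dose, and s0 and s1 the shares of events attributed to something other than PCA. Then:

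- counted rate = p × (1 − s)
- counted ratio = (p1 / p0) × (1 − s1) / (1 − s0)

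All values below are assumptions, because the documents give neither event rates nor shares.

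| p0, p1 | True ratio | s0, s1 | Counted rates | Counted ratio |
|---|---|---|---|---|
| 40%, 40% | 1.00 | 20%, 20% | 32%, 32% | 1.00 |
| 40%, 40% | 1.00 | 30%, 10% | 28%, 36% | 1.29 |
| 40%, 40% | 1.00 | 40%, 10% | 24%, 36% | 1.50 |
| 40%, 40% | 1.00 | 10%, 30% | 36%, 28% | 0.78 |
| 40%, 30% | 0.75 | 20%, 20% | 32%, 24% | 0.75 |
| 40%, 30% | 0.75 | 30%, 10% | 28%, 27% | 0.96 |
| 40%, 30% | 0.75 | 40%, 10% | 24%, 27% | 1.13 |
| 40%, 30% | 0.75 | 10%, 30% | 36%, 21% | 0.58 |

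Worked line: 0.40 × 0.70 = 0.28, 0.30 × 0.90 = 0.27, and 0.27 / 0.28 = 0.96.

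The factor (1 − s1) / (1 − s0) equals 1 only when the shares are equal. In that case the ratio is unbiased, but fewer events are counted and the absolute difference narrows (from 10 to 8 percentage points in the 20%, 20% line). With unequal shares the ratio moves, and its direction depends on which arm has the larger share.

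**The case against.** The strongest reply is that the phrase is loose description. Nothing in the article sets up an attribution step, names an adjudicator or says that any event is excluded. Table 2 has no field for cause, and the antiemetic provisions respond to nausea or vomiting without asking what caused it. Since every participant is on PCA, the wording may mean no more than nausea and vomiting while on PCA. The full protocol or the case report form may also settle how events are counted.

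Much of this stands. The documents do not show that events will be dropped, and the absence of an attribution rule from a condensed article is not in itself a fault. What remains is that the same limit appears in both the definition and the analysis text, while the schedule and the aim lack it. An analyst following the wording could restrict the count, and one following Table 2 would not.

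Three stronger readings are tempting, and the documents do not support them:

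- **The difference between arms must shrink.** That follows only if more events are attributed elsewhere on placebo. Patients in more pain may also press the PCA button more, which could raise attribution to PCA. Assessors are blinded to arm, so any differential has to work indirectly, through visible rescue use.
- **Nausea from the study drug is hidden.** Table 2 schedules nausea and vomiting at each postoperative assessment, and all adverse events are recorded, with causality reported. The data survive; what is missing is a named between-group comparison for events attributed elsewhere.
- **A loss of power shows arm-dependent loss.** Removing the same share of events from every arm lowers the counted rates and costs precision, but leaves the ratio unchanged. It is no evidence of bias.

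**Conclusion.** The point holds as an inconsistency in the definition of the secondary outcome. Read literally, the definition makes the endpoint depend on a subjective attribution after randomisation that can be influenced by another outcome of the trial. The counted event rate would then be lower than the all-cause rate, and the comparison could be biased either way.

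Neither size nor direction can be known from the document. The illustrated range (true ratio 0.75 counted as anything from 0.58 to 1.13; true ratio 1.00 counted as 0.78 to 1.50) rests wholly on assumed rates and on assumed shares that differ between arms. With equal shares the ratio is unbiased. If the phrase is only descriptive and every event is counted, there is no bias at all and only the wording is at fault.

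The primary outcomes and the sample size, which rests on PCA usage, are unaffected.

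**What to change.** In the abstract, in Outcomes and in the statistical methods, define the secondary outcome as any nausea or vomiting in each of the four periods up to 72 h, whatever the cause. This matches the row in Table 2 and the aim at the end of Outcomes. If attribution to IV PCA is still of interest, report it descriptively at most, and do not use it to decide which events enter the comparison.

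The cost is an edit in three places. Table 2 already provides for the data, and patient care is unaffected. The one thing given up is that the outcome becomes less specific to PCA.

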### Eligibility criteria

Patients undergoing spinal surgery for degenerative lumbar disorders will be recruited from the Department of Orthopaedic Surgery, at Ajou University Hospital. Identified patients will be approached for inclusion in the study based on the inclusion/exclusion criteria described below.

Inclusion criteria are as follows: age 19 years or older, patients undergoing spinal surgery for degenerative lumbar disorders, and voluntary agreement to participate in the study after receiving sufficient explanation.

Exclusion criteria are as follows: minors under the age of 19 years, patients assigned to American Society of Anesthesiologists classification class 3–6, previous frequent dizziness or headaches, active alcohol or drug usage, having taken any analgesics daily or within 48 h before surgery, impaired renal (glomerular filtration rate < 60 mL/min/1.73 m^2^) and/or hepatic function (Child Pugh classification B and C), diagnosed with and treatment for anxiety or depressive disorders, and coverage from worker’s compensation insurance or car insurance.

Patients with severe adverse reactions to our drug of interest, such as dizziness, drowsiness, or peripheral oedema, will be excluded. Patients with any postoperative complications including infection, nerve injury, hematoma, metal implant-related problems, and death, will also be excluded.

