## Data collection and management

### Plans for assessment and collection of outcomes

Data will be collected using case report forms (CRFs) on paper, which will be completed by trained CRAs from days 1 to 4. The schedule of assessments is shown in Table 2.

**Table 2 Tab2:** Schedule of patient enrolment, interventions, and assessments

**Time point**	Study period							
	Enrolment	Allocation	Post-allocation					
	D-14	D0	Surgery	1 h	6 h	24 h	48 h	72 h
**Enrolment:**	X							
Eligibility screen	X							
Informed consent	X							
Inclusion and exclusion criteria	X							
Allocation		X						

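### No pain score or symptom check is scheduled before the first study dose, which costs precision on VAS and blurs new against existing symptoms, but does not bias the randomised comparison

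*Protocol article*

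**What the plan says.** The abstract sets the dosing: "Each participant will be administered placebo or pregabalin once prior to surgery and every 12 h after surgery for 72 h". The Intervention description agrees.

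On measurement, the Outcomes section states: "Assessments of all variables will be performed during the first 72 h following the arrival of the participant at the general ward". It then describes the VAS analysis: "The pain levels in each time zone will be compared to see if they differ depending on the treatment method". Table 2, titled "Schedule of patient enrolment, interventions, and assessments", has columns D-14, D0, Surgery, 1 h, 6 h, 24 h, 48 h and 72 h. The rows for VAS, PCA use, rescue analgesia, nausea and vomiting, sedation, dizziness, headache, visual disturbance and swelling are marked only from 1 h onward. The text introducing the table says of the case report forms: "which will be completed by trained CRAs from days 1 to 4".

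The Statistical methods section names no covariate: "If the normality assumption is met, we will perform an analysis of variance (ANOVA) analysis; otherwise, we will use the Kruskal–Wallis test for comparison". Safety is compared by chi-squared on the "incidence of side effects (sedation, dizziness, headache, visual disturbance, and swelling"). Of these five symptoms, the Eligibility criteria name only two as pre-existing conditions that exclude a patient: "previous frequent dizziness or headaches".

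**The concern.** The 1 h reading comes after surgery and, by the text, after the first dose, so it cannot serve as a baseline. A later analysis plan can choose covariates, but it cannot recover a measurement that was not taken.

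Two things are at stake. For VAS, differences between patients that preoperative pain would explain stay in the error term. A chance difference in preoperative pain between small arms can be neither seen nor corrected, because randomisation is stratified by sex and age only. The plan also removes patients after randomisation (missing data, dropout, severe reactions, complications), so the analysed set is smaller than the randomised one, and preoperative pain would be a natural check that the completers remain comparable.

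For safety, which the Objectives put beside efficacy, incidence is compared with no stated rule separating new symptoms from existing ones.

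**Working it through.** **1. The plan's own sample size.** Inputs from the Sample size section, taken as stated: f = 0.448, alpha = 0.0167, power 0.95, four groups. One-way ANOVA power from the noncentral F distribution with noncentrality f² × N gives 28 per group, N = 112, power 0.9547. Then 28 / (1 − 0.15) = 32.9, so 33 per group and 132 in total. Both figures reproduce. They rest on PCA usage, not VAS, so nothing in the stated power depends on a baseline VAS.

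**2. What adjustment would be worth on VAS.** The article gives no correlation r between preoperative and postoperative VAS, so r is assumed over a range. Adjustment multiplies the error variance by 1 − r², so the effective number per arm is 33 / (1 − r²):

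| r (assumed) | Error variance removed | Effective n per arm |
|---|---|---|
| 0.2 | 4% | 33 / 0.96 = 34.4 |
| 0.3 | 9% | 33 / 0.91 = 36.3 |
| 0.5 | 25% | 33 / 0.75 = 44.0 |

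The one degree of freedom spent on the covariate is ignored.

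**3. Chance imbalance.** With 28 analysed per arm, the standard error of a between-arm difference in mean preoperative pain is √(2/28) = 0.267 SD. An imbalance of that size moves the unadjusted postoperative difference by r × 0.267: 0.053 SD at r = 0.2, 0.080 SD at r = 0.3 and 0.134 SD at r = 0.5. Across repeated trials these shifts average to zero. They are noise, not bias.

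**4. Side effects.** Let b be the proportion with the symptom before dosing, equal in all arms, and q the drug-related rate. The observed rate is 1 − (1 − b)(1 − q), so the difference between two arms shrinks by the factor 1 − b. For illustration, assume q = 10% against 35%, 28 per arm, two-sided 5%:

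| b (assumed) | Observed rates | Difference | Pairwise power |
|---|---|---|---|
| 0% | 10.0% v 35.0% | 25.0 points | 0.62 |
| 10% | 19.0% v 41.5% | 22.5 points | 0.45 |
| 20% | 28.0% v 48.0% | 20.0 points | 0.34 |
| 30% | 37.0% v 54.5% | 17.5 points | 0.26 |

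Background symptoms raise every arm and shrink the contrast. They do not create a drug effect.

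**5. Is the gap in the schedule real?** Three statements agree: the Table 2 rows start at 1 h, the Outcomes section places the assessment of all variables after ward arrival, and the forms are completed from day 1 to day 4. Table 2 also marks study drug only from 1 h, which conflicts with the preoperative dose in the abstract and the Intervention description. Those passages must be reconciled. On either reading, nothing is assessed before surgery.

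**The case against.** A reader might infer that the VAS comparison is invalid without a baseline. It is not. The outcome is postoperative pain between randomised arms, no change-from-baseline endpoint is planned, and adjustment adds only precision. At r = 0.2 the gain is about one patient per arm, and VAS is one of three primary outcomes. This stands and limits the point.

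A reader might also infer that pre-existing symptoms are counted as drug side effects. No section says so. Medical history is taken by interview (Data management), causality and timing are reported for adverse events (Adverse event reporting and harms), and incidence is compared with a blinded placebo arm. Frequent dizziness and headache are excluded. The ASA, renal, hepatic, alcohol or drug and psychiatric exclusions may remove some patients with swelling or sedation. What remains is dilution and inflated absolute rates. These safeguards do not close the gap: none specifies a pre-dose symptom record, and the chi-squared comparison is not made conditional on causality.

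Last, Table 2 is not exhaustive. It has no row for medical history and leaves out the preoperative dose. Fig. 1 is not shown, and the article condenses a fuller protocol, so a baseline recorded elsewhere cannot be ruled out. But Table 2 is the assessment schedule itself, and the Outcomes text agrees with it.

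**Conclusion.** The point holds as an improvement to the design. As the article stands, no VAS reading and no side-effect check is scheduled before the first dose. Postoperative VAS therefore cannot be adjusted for preoperative pain, and new symptoms cannot be reliably told from existing ones.

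The size on VAS depends wholly on the assumed correlation: between 0.2 and 0.5, the forgone adjustment is worth about 1 to 11 extra patients per arm on a base of 33. Imbalance from chance or from post-randomisation exclusions cannot be checked. For harms, the direction is towards diluted contrasts and higher absolute rates, mainly for sedation, visual disturbance and swelling, and less for dizziness and headache. The documents give no background rates, so the power figures above are illustration only.

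No stated figure is wrong on this account, and the randomised comparison is not biased by it.

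**What to change.** - **Schedule.** Add to Table 2, at the existing preoperative visit and before the first study dose, one VAS pain-ruler reading and the five side-effect items.
- **VAS analysis.** Compare postoperative VAS by ANCOVA with preoperative VAS as covariate, or by a rank-based ANCOVA if the data are clearly non-normal. This replaces the planned test for VAS, because Kruskal–Wallis takes no covariate.
- **Missing covariate.** The plan excludes patients with missing data. State that a missed preoperative reading does not by itself remove a patient, for example by filling the covariate with the overall mean.
- **Side effects.** Report incidence as symptoms new or worse than at the pre-dose check.

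The cost is a minute or two of staff and patient time, one CRF line and a changed test for VAS. Patients enrolled before the change would have no preoperative value, so the gain is largest if it is made early.
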